##### Qualitative Sample

The qualitative approach will be used to obtain data on perceptions and acceptability of the intervention among stakeholders. Qualitative data will be collected using focus group discussions (FGDs), in-depth interviews (IDIs), and key informants. A minimum of 6 FGDs will be conducted among men in relationships and among women of reproductive age, giving a cumulative total of at least 18 FGDs across all districts. Each FGD will comprise 7 to 9 participants. In each district, we will also conduct a minimum of 5 IDIs among CHEWs and 4 among clients. This gives a cumulative minimum total of at least 24 IDIs. In addition to the IDIs, we will conduct 5 key informant interviews (KIIs) per district involving health managers such as the district health officer, assistant district health officer in charge of maternal and child health, as well as health facility managers and supervisors. This will give a cumulative minimum total of at least 15 KIIs. An additional 8 KIIs will be conducted at the national level to obtain views from program managers and policymakers. However, data will be collected based on the concept of saturation.

### Sampling Procedure

#### CHEWs and Authorized Cadre: Noninferiority Design

Simple random sampling with replacement will be used to sample CHEWs to observe in each district. In each district, we will construct a sampling frame comprising all trained CHEWs. Simple random sampling (using a Microsoft Excel random number generator) with replacement will be used to identify individual CHEWs that will be observed. The authorized cadre will be selected using a similar approach. Where the number of authorized cadres is smaller than the estimated sample size, we will recruit from neighboring districts because the competence of the authorized cadre should not be dependent on the place where the health worker provides the services.

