### Sample Size Estimation

#### Quantitative Data

##### Sample Size Estimation: Noninferiority Design

CHEWs will be assessed on their competency to insert implants, under some domains with corresponding items, following training in the selected districts. The assessment of the competency of the CHEWs will be compared to the competency of the qualified health facility providers in the cadre currently authorized to insert implants. Competency will be measured on a continuous scale and summarized as mean (SD) scores. The competency of CHEWs should not be *worse than* that of the authorized cadre, within a margin of acceptable difference (-*d*_*NI*_), accounting for the mean (SD) score competency of authorized cadres (*μ*_*B*_) and that of CHEWs (*μ*_*A*_), and a 1-sided test.

We assumed an SD (*σ*^2^) of the competency scores, and the noninferiority limit (-*d*_*NI*_) was set at −10. At a power of 90% and 1-sided 95% CI, this resulted in a total of 138 participants (69, 50%, cadres authorized to provide implants and 69, 50%, CHEWs) needed to demonstrate that there is truly no difference between the competency of the cadres authorized and the trained CHEWs. We adjusted for a nonresponse rate of 10% and a design effect of 1.2 because multiple CHEWs selected from similar settings and cadres authorized selected from the same health facilities observations will be correlated. This adjustment will result in a minimum of (138×1.2)/0.9=184 (92 CHEWs and 92 authorized cadres).

Compared with a randomized trial, the noninferiority design is more appropriate for this evaluation because it would be a false assumption to randomize participants to receive the service by the CHEWs or the authorized cadre because the 2 groups are not comparable in terms of level of training and competencies. The authorized cadre has gone through formal training, which is not comparable with the training the CHEWs have received; therefore, the best approach for any comparison is such that the competencies of the CHEWs are noninferior or at most equal to the competencies of the authorized cadre.

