#### Competencies of the CHEWs to Insert Implants

We will measure the clinical competencies around implant insertion using an observation checklist. One observation will be made for each CHEW. For each CHEW, we will observe the process from counseling before the implant is inserted until the end, including postinsertion counseling. For each observable item, the CHEW will be marked as having performed the task as satisfactory, unsatisfactory, or not done. Satisfactory will mean that the step or task has been efficiently performed in its proper sequence or individually, unsatisfactory will mean that the task was not performed correctly or in sequence, and not done will mean the task was omitted or not performed, yet it was necessary. Satisfactory will fetch a mark, unsatisfactory will fetch 0.5, and not done=0. CHEWs will be considered competent if they score 80% and above.

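### Drawing providers with replacement conflicts with one observation per CHEW and with 92 separate people per group; depending on the unstated list sizes, repeats can cost power or understate the standard error

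*Protocol article*

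**What the plan says.** Three parts of the protocol article bear on this.

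- *Sampling Procedure, CHEWs and Authorized Cadre: Noninferiority Design*: "Simple random sampling with replacement will be used to sample CHEWs to observe in each district". The section repeats the with-replacement instruction when it describes the random number generator. For the comparator it says "The authorized cadre will be selected using a similar approach", and adds that neighboring districts will be used if there are too few authorized staff.
- *Study Variables, Competencies of the CHEWs to Insert Implants*: "One observation will be made for each CHEW".
- *Sample Size Estimation: Noninferiority Design*: "At a power of 90% and 1-sided 95% CI, this resulted in a total of 138 participants", with 69 per group. Adjustment for nonresponse and clustering "will result in a minimum of (138×1.2)/0.9=184 (92 CHEWs and 92 authorized cadres". The design effect is justified by correlation between different providers in similar settings or the same facility.

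The article does not give the length of any sampling list, the district quotas or the value of the SD. It has no rule for a provider drawn more than once, and does not say whether drawing stops at 92 draws or at 92 people.

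**The concern.** Under sampling with replacement, a provider who has been drawn goes back on the list and can be drawn again. With about 31 draws from a district list of moderate length, repeats are to be expected. There are then three ways to handle a repeat, and each breaks something the article states:

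- a second observation contradicts the one-observation rule for CHEWs;
- counting the single record twice puts a copy into the analysis as if it were a new person;
- dropping the repeat leaves fewer than 92 people.

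Dropping costs power. In a noninferiority comparison, counting copies as independent is the more serious error, because a standard error that is too small makes noninferiority easier to declare. Sampling without replacement from the same list avoids both problems.

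**Working it through.** **Inputs.** Power 90%, one-sided 5%, limit −10, true difference 0, nonresponse 10%, design effect 1.2 and 92 per group are from *Sample Size Estimation*. The SD is not given and is back-solved. An even split of draws over the three districts (31, 31, 30) and the list length N per district are assumptions, so results are shown over a range of N.

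**The plan's own figures.** With SD 20, n per group = 2 × (20/10)² × (1.645 + 1.282)² ≈ 68.5, so 69. An SD between 19.93 and 20.07 gives 69. Power at 69 per group = Φ(10 / (20 × √(2/69)) − 1.645) = Φ(2.937 − 1.645) = 90.2%. The inflation is 138 × 1.2 / 0.9 = 184 exactly. Run backwards, 92 × 0.9 / 1.2 = 69, so no margin is left for repeat draws.

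**Repeats dropped after 92 draws.** Expected distinct providers from k draws on a list of N = N × (1 − (1 − 1/N)^k), summed over the districts. Effective n = distinct × 0.9 / 1.2. Power = Φ(10 / SE − 1.645), with SE = 20 × √(2/n) if both groups are affected, or 20 × √(1/n + 1/69) if only CHEWs are.

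For N = 40:

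- distinct = 21.75 + 21.75 + 21.28 ≈ 64.8;
- effective n = 64.8 × 0.9 / 1.2 = 48.6;
- SE = 20 × √(2/48.6) = 4.06;
- power = Φ(2.46 − 1.645) = 79%.

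| Listed per district | Distinct of 92 | Power, both groups affected | Power, CHEWs only affected |
|---|---|---|---|
| 40 | 64.8 | 79% | 85% |
| 60 | 72.5 | 83% | 87% |
| 100 | 79.6 | 86% | 88% |
| 200 | 85.5 | 88% | 89% |
| 500 | 89.3 | 89% | 90% |

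If drawing continues until 92 different people are reached, effective n is 69 and power is 90.2%, as planned.

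**Repeats kept as separate, identical records.** With about 28 responders per district (31 × 0.9 = 27.9), the true variance of the group mean exceeds the naive one by a factor of about 1 + 27/N. The actual one-sided error at the −10 limit is then about 1 − Φ(1.645 / √(1 + 27/N)):

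- N = 40: factor 1.675, error about 10%;
- N = 100: factor 1.27, error about 7%;
- N = 200: factor 1.135, error about 6%.

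The planned error is 5%. This assumes that both groups are affected, that there is no other clustering and that the analysis ignores the provider.

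**The case against.** The strongest reply is that the article aims at people, not draws. It gives 92 and 92 as a minimum, and the random numbers serve to identify individual CHEWs. If the field team redraws whenever a name comes up twice, nothing is lost. That reading is reasonable, but it amounts to sampling without replacement, and the article says the opposite twice. The phrase is also hard to read as replacing nonresponders, because it stands beside a random number generator and nonresponse is already covered by the 10% inflation.

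Several limits on the concern do stand:

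- The one-observation sentence names CHEWs only. For authorized staff the conflict rests on the similar approach and on the count of 92. The neighboring-district rule would also lengthen that list, so the column with both groups affected may be pessimistic.
- At 200 or more listed per district, power stays within about 2 points of 90%. A high chance of at least one repeat is no measure of harm, since a single repeat costs almost nothing.
- The error inflation requires copying records, which the article does not say will happen. It is an alternative to the power loss, not an addition to it. *Quantitative Data Analysis* promises control for observer, facility and district. CHEWs are stationed at their supervising facility, so copies would normally fall in one facility cluster and part of the variance error could be absorbed. Lost providers would not be restored.
- With-replacement sampling can give a valid standard error for the mean of a fixed roster. The study's stated purpose, however, is to inform task shifting in Uganda and scale-up, which reaches beyond the listed providers.

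**Conclusion.** The inconsistency is real and lies in the article's own wording. Drawing with replacement, one observation per CHEW and 92 separate people per group cannot all hold once a name is drawn twice, and the sample size leaves no room for repeats.

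The consequence is conditional. If drawing stops at 92 draws and repeats are dropped in both groups, power is about 79% at 40 listed per district, rising to 89% at 500. These figures assume an SD of 20, an even district split, and the plan's own design effect and nonresponse. If repeats are counted as independent, the standard error is too small unless the clustering adjustment absorbs it.

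A reader might infer that the study is bound to have clearly fewer than 92 distinct providers per group and will miss its 90% power. The documents do not support that, because it depends on list lengths that are not stated and on there being no redraw to 92 people.

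**What to change.** - In *Sampling Procedure*, change with replacement to without replacement for both groups. Equivalently, state that repeats are redrawn until 92 distinct providers per group are reached.
- Where a district's CHEW list is shorter than its quota, take everyone on it and reallocate the shortfall to the other pilot districts. Keep the existing neighboring-district rule for authorized staff.
- If sampling is already done, report the number of distinct providers per group and how repeats were handled, redraw repeats where still feasible, and do not analyse a repeat as an independent participant.

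Before sampling, this costs only a change of wording. The abstract says data collection had started by August 2025 and was expected to end in October 2025, so there may now be a field cost. If repeats were dropped, restoring 92 would take about 12 further observed providers per affected group at 100 listed per district (92 − 79.6), and about 27 at 40 (92 − 64.8).

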#### Qualitative Sample

Purposive sampling will be used to identify key stakeholders engaged in family planning activities within the selected districts and at the national level. The respondents will be selected based on their knowledge and experience in offering family planning services. In total, we plan to conduct approximately 65 interviews across the selected intervention districts.

### Study Variables

#### Acceptability of the Community-Based Implant by CHEWs Among the Communities

Acceptability will be measured based on the constructs of the theoretical framework of acceptability [17]. These constructs include (1) affective attitude: how the stakeholders feel about the intervention; (2) burden: the perceived amount of effort that is required to participate in the intervention; (3) ethicality: the extent to which the intervention aligns with an individual’s value system; (4) self-efficacy: the participant’s confidence that they can perform the behaviors required to participate in the intervention; and (5) intervention coherence: the extent to which the participant understands the intervention and how the intervention works.

#### Perceived Effectiveness

Perceived effectiveness is the extent to which the intervention is perceived to be likely to achieve its purpose, and the opportunity costs refer to the extent to which benefits, profits, or values must be given up to engage in the intervention.

#### Perceptions of Community Members Toward the Use of CHEWs to Insert Implants

This is a qualitative variable. We will focus on both positive and negative opinions. We will analyze for convergence and divergence of perceptions.

#### Perceptions of Programmers and Policymakers Toward the Implant Provision Task Shifting to the CHEWs

This is a qualitative variable. We will generate both positive and negative opinions about how the stakeholders perceive the idea of task shifting implant provision to the CHEWs.

#### Competencies of the CHEWs to Insert Implants

We will measure the clinical competencies around implant insertion using an observation checklist. One observation will be made for each CHEW. For each CHEW, we will observe the process from counseling before the implant is inserted until the end, including postinsertion counseling. For each observable item, the CHEW will be marked as having performed the task as satisfactory, unsatisfactory, or not done. Satisfactory will mean that the step or task has been efficiently performed in its proper sequence or individually, unsatisfactory will mean that the task was not performed correctly or in sequence, and not done will mean the task was omitted or not performed, yet it was necessary. Satisfactory will fetch a mark, unsatisfactory will fetch 0.5, and not done=0. CHEWs will be considered competent if they score 80% and above.

### Data Collection Methods

#### Quantitative Data Collection

The quantitative data will be collected through observations among CHEWs and authorized cadres inserting implants as part of the noninferiority assessment. The observation data will be collected using an observation checklist that was developed based on the implant insertion curriculum. The observation data will be used to quantitatively assess competence during the insertion of implants.

#### Qualitative Data Collection

##### Key Informant Interviews

KIIs will be conducted among health workers engaged in the intervention as either trainers or supervisors of the CHEWs, as well as representatives of organizations engaged in provision of long-term reversible family planning. Additionally, those at the policy level, such as district health officers and family planning experts at the Ministry of Health, will be included.

##### Focus Group Discussions

FGDs will be conducted among CHEWs to elicit opinions and perceptions about engaging CHEWs in implant insertion. Additional data about the acceptability of the intervention will also be collected using this approach. The FGDs will comprise 7 to 9 participants. Data will be collected using an FGD guide. Data will be collected in the predominantly spoken local languages, specifically Lango (Lira), Luganda (Kyotera), and Lusoga (Namutumba). All discussions will be audio recorded after obtaining consent.

##### In-Depth Interviews

IDIs will be conducted with CHEWs engaged in the intervention and clients who have had implants inserted by the CHEWs. These interviews will focus on getting individual insights, opinions, and perspectives about the acceptability, feasibility, and quality of services received. They will also generate insights into the experiences during the procedure. The IDIs will be conducted using in-depth guides that have been translated into Langi, Luganda, and Lusoga after obtaining informed consent.

### Data Management

#### Quantitative Data

Quantitative data will be collected on smartphones using electronic questionnaires programmed with Open Data Kit software. Back-to-back encryption will be implemented to protect the respondents’ data. A routine data quality assessment check will be carried out on a daily basis. The IT administrator will check the data received at the server for extreme values, incompleteness, and incorrectly entered fields. A report will be generated based on these findings and immediately communicated to the regional team leaders through the survey coordinator. The final datasets will be uploaded to MakSPH’s secure and password-protected server after cleaning. The data manager and IT administrator will download data from the server and export it to R Software (R Development Core Team) for analysis after necessary cleaning.

#### Qualitative Data

All audio interviews will be transcribed verbatim from the local language to English. In cases where the participants turn down the request to audio record the discussions or interviews, notes will be taken and expanded immediately to enrich the transcripts.

### Data Analysis

#### Quantitative Data Analysis

Quantitative data will be cleaned and analyzed using STATA (version 15), through univariate, bivariate, and multivariate analyses using appropriate statistical tests. For example, the chi-square test for independence will be used to assess whether CHEWs differ from the authorized cadre in the performance of specific tasks involved in the process of inserting implants. The chi-square test is computed based on the null hypothesis that the proportion of CHEWs who perform a specific task is equal to the proportion of the authorized cadre who perform that task. This hypothesis is rejected at a *P* value of .04. The chi-square test statistic is also computed with the assumption that all observations are independent, and therefore, the analysis will control for factors such as the observer, the health facility, and the district that might cause dependence or clustering of observations. Findings will also be presented as proportions, in tables and figures, odds ratios or prevalence ratios, and *P* values at a 95% confidence level.

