## Discussion

### Anticipated Implications

We will discuss the findings and their implications for improving access to family planning services at the community level. We anticipate that in general, the competence of CHEWs in insertion of implants will not differ significantly from that of the authorized cadre. We will compare how task sharing has been used for other service delivery, such as community case finding during integrated management of childhood illnesses, to identify lessons to inform family planning provision. For example, policymakers in Kenya noted concerns about the policy framework within which community health workers can distribute drugs at the community level and how this might affect the delivery of vertically oriented programs [18]. Conversely, task shifting in maternal and child health service delivery has the potential to reduce the workload on authorized cadre to spend more time on tasks that require more advanced training [19].

We will also compare our findings with similar approaches in Burkina Faso [20], Kenya [21], Ethiopia [10], Ghana [22], and Nigeria [11]. In Burkina Faso, health providers, community representatives, government officials, and clients were generally agreeable with the idea of implants being provided by trained community health workers [20]. However, community health workers in Burkina Faso were trained to provide several family planning options in addition to the implants. In Kenya, 95% of 434 respondents agreed that task sharing can increase and expand access to family planning services. It was found to benefit both clients and health service providers, particularly where the community health workers were provided with training, support supervision, and conducted within the requisite policy environment [21]. Similarly, qualitative findings from Ghana revealed that community health nurses could provide safe intrauterine devices to clients if they were well trained and provided with the requisite resources and technical support supervision [22].

Findings will also be compared with other studies that used similar noninferiority designs that assessed for safety, quality, and acceptability of community health workers providing the implants in rural settings [23]. We will also discuss other factors to be considered before scale-up, such as the influence of the fact that the services are provided by CHEWs on cost, method choice, and uptake [24], and the broader impact on health system performance [25].

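### The only test the analysis section specifies is task-by-task equality; the one-sided comparison of mean score with −10 that sized the study is not carried into it

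*Protocol article*

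**What the plan says.** All references are to the protocol article.

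- **Sample Size Estimation: Noninferiority Design.** The endpoint is a score: "Competency will be measured on a continuous scale and summarized as mean (SD) scores". The comparison is one-sided, CHEWs against the authorized cadre, with a noninferiority limit of −10. The size is fixed "At a power of 90% and 1-sided 95% CI", giving 69 per group, then "92 CHEWs and 92 authorized cadres" after inflation. The same paragraph says the participants are "needed to demonstrate that there is truly no difference between the competency of the cadres authorized and the trained CHEWs". The next paragraph describes the target as CHEWs being noninferior or, at best, equal.
- **Quantitative Data Analysis.** After a general commitment to univariate, bivariate and multivariate methods with suitable tests, one test is given as an example: a chi-square test of independence for each task. Its hypothesis is the "null hypothesis that the proportion of CHEWs who perform a specific task is equal to the proportion of the authorized cadre", rejected at P=.04. The results listed are proportions, odds or prevalence ratios, and P values. The section says the analysis will control for observer, facility and district.
- **Anticipated Implications.** The authors expect that "the competence of CHEWs in insertion of implants will not differ significantly from that of the authorized cadre".

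The Abstract, Study Design, and Strengths and Limitations sections all present noninferiority as the defining quantitative design.

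**The concern.** The sample-size section and the analysis section pose different questions. They differ in endpoint (mean score or the proportion performing a task), in null hypothesis (a deficit of at least 10, or equality), in sidedness, and in level (one-sided .05 or P=.04). The analysis section is not merely silent: it writes out a null hypothesis and a rejection level, and they belong to the other question.

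This matters because the two kinds of test respond to weak data in opposite ways. A noninferiority test puts the burden on the data to exclude a deficit of 10. An equality test is more likely to be non-significant when data are few or noisy. Set beside the no-difference wording in the sample-size and discussion sections, a non-significant result could be read as support for task shifting when a deficit of 10 has not been excluded. An equality test can also flag a task on which CHEWs differ when the overall score is well within the margin. The findings are meant to inform scale-up of implant provision by CHEWs.

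**Working it through.** **Inputs from the article.** Margin 10; 90% power; one-sided 95% confidence; 69 per group before inflation; 10% nonresponse and design effect 1.2 ("We adjusted for a nonresponse rate of 10% and a design effect of 1.2"); chi-square rejection level .04.

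**Assumptions.** No value is given for the SD. The true difference used for sizing is taken as 0. The margin is read as points on a 0–100 score, since its unit is not stated.

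**Step 1. Reproduce the sample size.**

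n per group = 2·SD²·(1.645 + 1.282)² / 10².

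With SD = 20: 2 × 400 × 8.564 / 100 = 68.5, rounded up to 69, so 138 in total. Any SD from 19.93 to 20.07 gives exactly 69. Inflation: 138 × 1.2 / 0.9 = 184, as stated. Conversely, 92 × 0.9 / 1.2 = 69 effective per group. The stated size is therefore consistent with a noninferiority test of means, but only with an SD that the article does not give. At one-sided .025 an SD of about 18 would be needed instead.

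**Step 2. The noninferiority test on that sample.**

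SE = 20 × √(2/69) = 3.405. The lower bound exceeds −10 when the observed difference exceeds −10 + 1.645 × 3.405 = −4.40. The probability of passing is 90.2% at a true difference of 0 and 5.0% at a true difference of −10.

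**Step 3. An equality test on the same mean score.** The article does not plan this test. It is used here to compare the two hypotheses on one scale, borrowing the .04 level from the chi-square test. The two-sided critical value is 2.054, so an observed deficit under 2.054 × 3.405 = 6.99 is non-significant.

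| True difference | Equality test non-significant at .04 | Noninferiority test passes |
|---|---|---|
| 0 | 96% | 90% |
| −5 | 72% | 43% |
| −8 | 38% | 15% |
| −10 | 18.9% | 5.0% |

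At −10 the calculation is Φ(2.054 − 10/3.405) = Φ(−0.883) = 0.189; at the .05 level it is 0.164. Observed deficits between 4.40 and 6.99 are non-significant yet fail noninferiority.

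**Step 4. Sensitivity at a true difference of −10, level .04.** The noninferiority test stays at 5% throughout.

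- SD varied, 69 per group, Φ(2.054 − 10/SE): SD 15, SE 2.554, 3%; SD 18, SE 3.065, 11%; SD 20, 19%; SD 25, SE 4.256, 38%.
- Number per group varied, SD 20: 69 gives 19%; 35 gives 48.5%; 20 gives 68.2%.

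The error of reading non-significance as reassurance grows as information shrinks. It is not always above 5%: at SD 15 it falls below.

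**Step 5. The task-level test that is stated.** Illustrative task rates (assumed, not from the article), a 10-point deficit, 92 per group, unadjusted for clustering, level .04. Non-significant in 56% of studies for 90% against 80%, 69% for 80% against 70%, and 42% for 95% against 85%. With 69 per group: 66%, 76% and 54%.

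**The case against.** The strongest reply is that nothing in the analysis section excludes the mean-score comparison. The chi-square test is offered as an example among suitable tests and is confined to specific tasks, and it is not called primary. The sample-size section already fixes the score, the margin, the direction and the one-sided 95% interval, so comparing a lower bound with −10 follows naturally. Task-level tests and an overall noninferiority test can coexist. A journal article condenses a fuller protocol, and an analysis plan that is not shown may hold the missing statement.

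Much of this stands. A reader might infer that the noninferiority question will never be tested; the article does not support that. A reader might also infer that a non-significant difference will be counted as success. No section sets such a rule: the remark under Anticipated Implications is an expectation, and the no-difference phrase sits in the sizing sentence, where it can be read as loose wording for an assumed true difference of 0. It also stands that the SD and the task rates are assumptions, and that the article attaches .04 only to the chi-square test.

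What does not stand is the claim that this is only an omission. The section gives a specific hypothesis, level and set of outputs, and none of them relates to the quantity that sized the study.

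**Conclusion.** The point holds in this limited form: the analysis that the article specifies does not answer its noninferiority question, and its no-difference wording describes something that a non-significant equality test cannot show. This mismatch rests on the text alone and needs no assumed figure.

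Its size is illustrative. With an SD of 20 and 69 effective per group, non-significance at a true deficit of 10 would occur in about 19% of studies, against a 5% false pass under noninferiority. Over SDs of 15 to 25 the first figure runs from 3% to 38%. What does not depend on the SD is that only the noninferiority test holds its error at 5% whatever the precision. The sample size itself is not called into question by this point.

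**What to change.** 1. In Quantitative Data Analysis, state the primary analysis: the difference in mean competency score, CHEW minus authorized cadre, from a model that accounts for the clustering the section already mentions. Declare noninferiority only if the lower one-sided 95% confidence bound is above −10.
2. Label the task-level comparisons secondary or descriptive. Report differences in proportions with confidence intervals, and say that a non-significant P value will not be read as equality.
3. In the sample-size section, replace the phrase "needed to demonstrate that there is truly no difference between the competency of the cadres authorized and the trained CHEWs" with wording about excluding a deficit of 10 or more. There and in the Abstract, drop the wording that limits CHEWs to equality at best.
4. Under Anticipated Implications, express the expectation in terms of the margin, not the absence of a significant difference.

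The cost is wording only, with no extra participants or data. Under the assumed SD of 20, the planned numbers give about 90% power for this analysis at a true difference of 0.

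### The task-level chi-square tests are rejected at P=.04 without a reason, while the same paragraph reports at 95% confidence, so P values between .04 and .05 are classified two ways

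*Protocol article*

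**What the plan says.** Two sections of the protocol article set error levels.

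- **Quantitative Data Analysis.** The chi-square test of independence is offered as an example of the tests to be used. Its null hypothesis is that equal proportions of CHEWs and authorized cadre perform a specific task. The decision rule is: "This hypothesis is rejected at a *P* value of .04". The paragraph closes by saying that findings will be shown as proportions, odds or prevalence ratios, and P "values at a 95% confidence level".
- **Sample Size Estimation: Noninferiority Design.** This section concerns a different quantity, the mean competency score. It specifies a margin of -10 "and a 1-sided test", and states: "At a power of 90% and 1-sided 95% CI, this resulted in a total of 138 participants". After inflation for design effect and nonresponse the total is 184 ("92 CHEWs and 92 authorized cadres").

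Neither section says why .04 was chosen. The analysis section does not mention the margin or the one-sided bound.

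**The concern.** A significance threshold and a confidence level are two statements of the same error rate, and here they disagree within one paragraph. The analyst of a task with P=.045 has two instructions. Under the first, equality is not rejected. Under the second, the 95% interval for the difference will in general exclude equality and the result is significant. The choice could be made after the result is seen.

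The direction also matters. The null hypothesis is equality, and Anticipated Implications in the Discussion expects no significant difference between the groups. For a study hoping to find no difference, a stricter threshold is not the cautious choice: it makes the hoped-for result slightly easier to obtain. The sample-size section adds to the risk of misreading by saying that the sample is meant to show "truly no difference between the competency of the cadres authorized and the trained CHEWs". A non-rejected chi-square test could be taken as that demonstration, although it shows neither equality nor noninferiority.

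**Working it through.** **1. Which level governs which test**

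| Level | Where stated | What it governs |
|---|---|---|
| One-sided 95%, margin -10 | Sample Size Estimation | Noninferiority of the mean score |
| P=.04 | Quantitative Data Analysis | Equality of task-level proportions |
| 95% confidence | Quantitative Data Analysis | Presentation of proportions, ratios and P values |

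Only the last two apply to the same results.

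**2. Size of the mismatch.** The 2x2 chi-square test is two-sided.

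- alpha = .04: confidence 1 - .04 = 96%, critical z = 2.054.
- alpha = .05: confidence 1 - .05 = 95%, critical z = 1.960.

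The zone of conflict is .04 < P < .05. If the two groups truly perform a task equally often, P falls there with probability about .05 - .04 = .01.

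**3. The same zone when the groups differ.** The document gives no task-level proportions, so those below are assumptions. Effective n per group is 92 x 0.9 / 1.2 = 69. With p the mean of p1 and p2,

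power = Phi{ [ |p1 - p2| sqrt(n) - z sqrt(2p(1-p)) ] / sqrt(p1(1-p1) + p2(1-p2)) }.

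For 90% against 80% at .05: [0.1 x 8.307 - 1.960 x 0.505] / 0.5 = -0.318, which gives 37.5%.

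| Assumed proportions | Power at .04 | Power at .05 | Difference |
|---|---|---|---|
| 90% v 80% | 34.0% | 37.5% | 3.5 points |
| 90% v 75% | 60.7% | 64.3% | 3.6 points |
| 90% v 70% | 81.9% | 84.3% | 2.4 points |

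With a true 10-point gap on a task, equality would go unrejected 62.5% of the time at .05 and 66.0% at .04. The threshold changes little. The high non-rejection rate under either threshold is why non-rejection cannot stand as evidence for the CHEWs.

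**4. Is the sample size touched?** The plan's figure comes first. The article prints no value for the SD, so 69 per group cannot be reproduced from its inputs alone. With n per group = 2 SD^2 (z.95 + z.90)^2 / 10^2 and an assumed SD of 20:

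2 x 400 x (1.645 + 1.282)^2 / 100 = 68.5, rounded up to 69, or 138 in total.

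SDs from about 19.93 to 20.07 return 69; an SD of 15 gives 39 and an SD of 25 gives 108. The inflation step is exact: 138 x 1.2 / 0.9 = 184.

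Power check at SD 20: SE = 20 x sqrt(2/69) = 3.405, and Phi(10/3.405 - 1.645) = 90.2%. The .04 enters none of these steps, so replacing it with .05 leaves 138, 184 and 90% as they are.

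**The case against.** The strongest defence is that the defect is one number in a sentence offered as an example, in an article that condenses a fuller protocol. It concerns task-level comparisons for which the study was not sized, and the main comparison is specified elsewhere: continuous mean score, margin -10, one-sided, 95%. All of that stands, and it sets the severity. It does not remove the contradiction, because .04 is stated rather than omitted and conflicts with another statement in the same paragraph.

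A reader might infer more: that three incompatible error rates compete for one decision, that the noninferiority threshold is therefore undefined, and that the 90% power fails. Moving the other levels onto the mean-score test (SD 20 assumed, 69 effective per group) would give power of 88.2% at one-sided .04, 83.6% on a two-sided 95% interval and 81.1% at two-sided .04. Without an assumed SD, taking 90% as exact at one-sided .05, the figures are 88.0%, 83.3% and 80.9%. The arithmetic is correct, but no sentence in the article applies .04 or a two-sided 95% interval to that test. A one-sided 5% noninferiority test can sit beside 95% reporting of other results without conflict.

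That the analysis section does not repeat the noninferiority rule is not an error in itself; a fuller plan may well contain it. Repeating the rule there is still sensible, because the only test the section names is one of equality.

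**Conclusion.** Wrong as written; minor severity. The analysis section gives two levels, .04 and .05, for the same task-level results and no reason for the first. The effect is limited to P values between .04 and .05: about 1 test in 100 under equality, and 2.4 to 3.6 in 100 under the assumed differences, which are illustrative because the article states no task-level proportions.

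The noninferiority comparison keeps its own rule, its 90% power and its 184 participants. That conclusion rests on where each level is stated and does not depend on the assumed SD of 20.

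Whether .04 is a misprint for .05 or a deliberate choice cannot be told from the document. If it was deliberate, the reason is missing and the reporting level should have been 96%.

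**What to change.** 1. In Quantitative Data Analysis, replace .04 with .05 and state that the task-level tests are two-sided, to match the 95% confidence level used for reporting.
2. Label the task-level comparisons secondary, and add one sentence saying that failure to reject equality will not be read as evidence of noninferiority.
3. Carry the sample-size section's rule into the analysis section: noninferiority is concluded if the lower one-sided 95% confidence bound for the mean-score difference, CHEWs minus authorized cadre, is above -10. This is the same as the lower limit of a two-sided 90% interval.

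The cost is a few lines of text, with no change to the sample size, the stated power or data collection. The article reports that data collection had started by August 2025 and places analysis in November 2025, so the wording should be settled before anyone examines the task-level results.
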